### Sequence generation and allocation

To avoid contamination due to personnel turnover, the entities were grouped into 20 clusters according to geographical nearness and personnel sharing procedures. Clusters were stratified according to their characteristics:

• Couples of one emergency service and one emergency room (usually working together in the same geographical area) (n°10)

• Groups of emergency services (n°6)

• Only emergency rooms (n°4).

Clusters were attributed sequential numbers and sample function of STATA 7 (StataCorp LP 2005) was used to generate random numbers. We utilized the Italian lottery extracted number of 6th November 2004 in Rome as seeds number for generating the random sequences.

### Data collection

To assess the impact of the adoption of the clinical pathway over the current practice, we will analyse the data currently available from the actual information systems and no additional information will be collected.

In this way, emergency health workers will not be charged with extra work deriving from registration of ad-hoc information, and they will be completely devoted to the implementation of the pathway itself.

The Agency of Public Health created and maintains the Information System of Emergency Rooms (ISER), the Stroke Surveillance System (SSS) and the Hospital Information System (HIS) sufficient to obtain data for measuring the outcomes. Moreover the Agency for Public Health has access to the Information System of ES 118 (IS118).

### Data analysis

• Baseline characteristics of the entities will be compared to ensure randomisation success;

• Analysis will be performed in an Intention to treat basis;

• Other analysis by protocol will be performed as a sensitivity analysis;

• Preliminary analysis will be performed after three month of the beginning of the observation.

All the analysis will be processed with SAS (version 8) and STATA 7 (StataCorp LP 2005).

### Ethics

The present protocol was designed following the indication of Helsinki adopted by the 18th World Medical Association General Assembly in June 1964 and following amended in 1975–2002 and clarified respectively for paragraph 29–30 in 2002 and 2004. The ethical committee of the Agency for Public Health approved the protocol with the document n.124 of 15 June 2004. The ethical committee was created according to Helsinki indications including, among others, a member of a patients' rights organization.

An informed consensus was signed by the responsible of each entity participating in the study who received a document containing all the relevant information and copies of the clinical pathway and the study protocol. No informed consensus will be requested to patients [7].

### Stopping rules

The nature of the intervention to be experimented prevented us from identifying specific stopping rules and we could only commit ourselves to submitting any possible problems to the ethical committee. The core of the pathway consists of transferring patients likely to benefit from complex interventions to specialized structures, rather than providing them with minimal assistance in the nearest hospital. This means that health workers belonging to experimental clusters may need to transfer patients for longer distance than they used to do. The risks we can foresee are unexpected events during transportation and troubles deriving from the unavailability of ambulances. Health workers have been warned to promptly report any kind of problems to the study coordinator.

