### Outcomes

The outcomes relate to organizational aspects (transportation to the appropriate hospital, accurate diagnosis and interventions, timely treatments) and will be measured as:

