#### Primary outcome

- proportion of patients with a positive CT for ischaemic stroke and symptoms onset <= 6 hour admitted to the stroke unit

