#### Secondary outcomes

- proportion of patients with a positive CT for hemorrhagic stroke and symptoms onset <= 6 hour admitted to a neurosurgical ward

- proportion of patients with a positive CT for hemorrhagic or ischaemic stroke or symptoms onset >6 hour admitted to the nearest hospital

- proportion of ICD9CM code for stroke in emergency setting confirmed in the hospital discharge data

- proportion of patients with stroke confirmed by CT results

- proportion of patients with ischaemic stroke receiving treatment within 6 hour of symptoms onset

All the outcomes will be reported at cluster level and will be cross-checked by the integration of data from the available information systems.

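### As planned, the trial makes no comparison by arm of the transport harm it foresees: harm rests on spontaneous reports, and none of the six listed outcomes counts a death or a transport event

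*Protocol article*

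**What the plan says.** The Stopping rules section of the protocol article explains how harm could arise: "health workers belonging to experimental clusters may need to transfer patients for longer distance than they used to do". It then names what is expected: "The risks we can foresee are unexpected events during transportation and troubles deriving from the unavailability of ambulances". No stopping rule is set. The two safeguards are reporting by staff ("Health workers have been warned to promptly report any kind of problems to the study coordinator") and referral ("we could only commit ourselves to submitting any possible problems to the ethical committee").

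The Outcomes section sets the scope: "The outcomes relate to organizational aspects (transportation to the appropriate hospital, accurate diagnosis and interventions, timely treatments"). The primary outcome is the "proportion of patients with a positive CT for ischaemic stroke and symptoms onset <= 6 hour admitted to the stroke unit". The five secondary outcomes cover two further admission destinations, confirmation of the emergency stroke code at discharge, confirmation by CT, and the "proportion of patients with ischaemic stroke receiving treatment within 6 hour of symptoms onset".

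The Data collection section rules out collecting anything beyond the existing information systems (ISER, SSS and HIS, with access to IS118) and calls them "sufficient to obtain data for measuring the outcomes". The Data analysis section plans a preliminary analysis at three months and gives it no safety content. The Background says the results will inform the decision on region-wide adoption.

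**The concern.** The authors identify a specific way in which the intervention could hurt patients, then choose outcomes that do not measure it. Spontaneous reports have no stated event definition, denominator or comparison by arm. The staff who make them know their allocation. The Discussion adds that participating workers fear legal consequences from decisions made under the study, which is a reason to under-report. Counts from such a source could be biased in either direction and cannot be read as a contrast between arms.

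The primary outcome adds a second difficulty. If its denominator is CT-positive patients, a patient who dies in transit or before CT leaves the analysis and is not counted as a failure. Analysis by intention to treat at cluster level does not bring that patient back.

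At stake is a roll-out decision resting on better process figures, with the foreseen harm never compared. The Ethics section says that patients will not be asked for consent, which makes the gap harder to accept.

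**Working it through.** **Step 1. Foreseen harm against planned measurement.**

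| Item | Where | Does it count a death, transport event or ambulance delay? |
|---|---|---|
| Stroke unit admission, CT-positive ischaemic, onset within 6 h | Primary outcome | No |
| Neurosurgical admission, CT-positive haemorrhagic, onset within 6 h | Secondary outcomes | No |
| Admission to the nearest hospital | Secondary outcomes | No |
| Emergency stroke code confirmed at discharge | Secondary outcomes | No; an early death might appear as a non-confirmation |
| Stroke confirmed by CT | Secondary outcomes | No; the same, if the denominator is all suspected strokes |
| Treatment within 6 h of onset | Secondary outcomes | No; it reflects delay indirectly |
| Staff reports | Stopping rules | Possibly, but with no definition, denominator or comparison by arm |

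**Step 2. Effect of losing early deaths from a CT-positive denominator.** The figures are hypothetical: arm 1 would have 70 of 100 admitted to the stroke unit, and five patients die before CT.
- All five would have been admitted: 65/95 = 68.4%, below 70%. Scored as failures they give 65/100 = 65%.
- None of the five would have been admitted: 70/95 = 73.7%, above 70%. Scored as failures they give 70/100 = 70%.

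Dropping the deaths always gives a higher proportion than scoring them as failures. Against the proportion without the deaths, the direction depends on who is lost.

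**Step 3. The plan's own figure.** No safety quantity is stated, so there is none to reproduce. The 95% power in Sample size concerns correct transfer only. For emergency rooms (14 clusters of 55, 14% v 35%, ICC 0.05):
- design effect = 1 + 54 × 0.05 = 3.7;
- effective n per arm = 7 × 55 / 3.7 = 385 / 3.7 = 104;
- two-sided power = 94.6%, which agrees with the stated 95%.

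**Step 4. Precision of a mortality comparison on the same clusters.** Inputs: 10% mortality (Background, 30-day figure for ischaemic stroke, used as a stand-in); 14 emergency room clusters of 55 (Sample size), assumed to split 7 v 7, so 385 patients per arm; ICC for death assumed between 0.01 and the plan's 0.05; t(0.975, 12 df) = 2.179.

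Half-width = t × √(2 × 0.1 × 0.9 × DE / 385), with DE = 1 + 54 × ICC.
- ICC 0.01: DE = 1.54; 2.179 × √(0.2772 / 385) = 2.179 × 0.0268 = 5.8 points.
- ICC 0.05: DE = 3.7; 2.179 × √(0.666 / 385) = 2.179 × 0.0416 = 9.1 points.

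**Step 5. Detectable harm.** Take the 750 expected patients, assume an equal split (375 per arm, about 37 to 38 control deaths at 10%) and clusters of 25 or 37.5, with a normal approximation on the effective sample size.

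| ICC | Effective n per arm | Power, 10% v 15% | Arm 1 mortality detectable with 80% power |
|---|---|---|---|
| 0 | 375 | 54% | about 17% |
| 0.01 | 275 to 302 | 43 to 46% | about 18% |
| 0.05 | 133 to 170 | 23 to 29% | about 21 to 23% |

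**The case against.** The strongest reply is that this is an implementation trial with deliberately organisational outcomes. A fuller protocol also exists, since participating entities received it, and reporting procedures may be set out there. That stands for event definitions and forms. It does not answer the main point, because the article lists its outcomes explicitly and excludes further data collection. Those are stated decisions and not the effect of condensation.

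Four stronger readings are tempting, and the documents do not support them.
- **Only arm 1 reports harm.** The article does not restrict the warning to arm 1. Unequal reporting is plausible among unblinded staff, but it is an inference.
- **Dropping early deaths inflates the arm 1 result.** Step 2 shows that the proportion can also fall. The denominator itself is a natural reading and is not spelled out.
- **The trial is incapable of showing harm.** This holds only for the trial as planned. The linked systems may hold vital status.
- **A mortality outcome is certain to need no new data.** The article calls the systems adequate for the listed outcomes. It does not say that they record death, and the Discussion admits uneven recording.

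Two further objections stand and shape the fix. Only arm 1 is trained to recognise suspected stroke, so that group depends on arm: arm 1 may flag more or milder cases and so dilute its mortality. And the added comparison would be imprecise, so a wide null result could reassure falsely.

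**Conclusion.** The concern holds for the trial as planned. Harm from longer transport is foreseen, captured only by spontaneous unblinded reports passed to the coordinator and the ethical committee, and absent from all six outcomes. No comparison by arm of that harm is planned. On the natural reading of the primary outcome, a death before CT is removed and not scored as a failure; the direction of the effect on arm 1 is undetermined.

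A mortality comparison would have a 95% half-width of about 6 to 9 percentage points. This rests on 10% mortality, a 7 v 7 split of emergency room clusters of 55, and ICC 0.01 to 0.05. The 10% is a 30-day figure for ischaemic stroke; death before arrival or in hospital among all suspected strokes may differ, and the half-width scales with √(p(1 − p)). Emergency room clusters are used although the named harm arises in ambulances, so the figure shows the order of precision only.

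This is a design improvement the sponsor should make. It does not invalidate the planned process comparison.

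**What to change.** 1. Confirm that IS118, ISER and HIS record death before or at emergency room arrival and in-hospital death, in the same way in both arms.
2. If so, prespecify these deaths as a descriptive safety outcome, analysed by originally randomised cluster and reported by arm with a cluster-adjusted confidence interval.
3. Do not rely on staff-flagged suspected stroke as the only denominator. Also report the outcome with one that depends less on arm-specific recognition, for example patients with a discharge diagnosis of stroke plus deaths before or at arrival. Report the numbers identified in each arm.
4. State in advance that precision is about ±6 to ±9 points under the assumptions above, that only a large harm could be exposed, and that a null result is not evidence of safety.
5. State the denominator of the primary outcome and how deaths before CT are handled.
6. Keep spontaneous reports as a supplement.

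The cost is one additional outcome and its analysis, plus the check on the data sources. If the systems do not record these deaths, the cost is higher, because some added data collection or linkage would be needed. A mortality outcome will not capture every foreseen problem: ambulance unavailability for other calls, for example, would still rest on reports.

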## Discussion

The emergency and pre-hospital field has not been studied sufficiently in randomised controlled trials, likely reasons are organizational difficulties, critical conditions of patients and the related ethical problems [8].

We are therefore pioneering this kind of study in a difficult environment and we are prepared to face many obstacles. First, there are the changes in the network of the emergency services. During the last twelve months many new entities were created and others were suppressed generating problems in the identification of clusters. Lack of personnel and high turnover increase risk of contamination due to personnel sharing during the summer and the holydays.

Other problems have to do with the local law imposing that patients taken from the scene should be brought to the nearest hospital where the emergency physicians will determine the need (opportunity) to transfer elsewhere for appropriate cure. This procedure delay interventions and determines a very low percentage of cases directly admitted to the stroke unit: 14% of the ambulances transport (calls), and 47% of the emergency room admissions. However health workers participating in the experimentation expressed their worry about possible legal consequences of their decisions caused by the implementation of the protocol study, and this may represent an important obstacle to adherence.

Accuracy of data registration is crucial for process evaluation but our quality control system revealed that, even though a priori criteria for data collection are homogeneous, results are sometimes heterogeneous. Nevertheless, as misreporting is non differential the deriving underestimation may not severely affect results.

## Abbreviations

CME = continuous medical education

CT = computer tomography

ES = Emergency Service

ER = Emergency Room

ALS = Advanced Life Support

BLS = Basic Life Support

CHSS = Cincinnati pre-Hospital Stroke Scale

ICD9CM = International Classification Diseases 9^th ^revision Clinical Modification

ICC = intra cluster correlation

ISER = Information System of Emergency Rooms

SSS = Stroke Surveillance System

HIS = Hospital Information System

IS118 = Information System of ES 118
